#### Consent and procedure

The schedule of enrolment, intervention and assessment is detailed in Fig. 1. Study recruitment will be open for a maximum of 8 months (Fig. 2) or until the sample size (enrolled) is reached. Participation (from study entry to exit) will be for a duration of 6 months.

People with diabetes who are interested in participating will be directed to the study website to access the Plain Language Statement and provide informed consent. After providing consent, they will complete screening questions. Eligibility will be determined automatically based on responses. Those eligible will complete an online baseline assessment (T0) (hosted by Qualtrics™) and, will be randomly allocated to one of two study arms. Those who are ineligible will be informed immediately using an autogenerated message and provided with links to resources for mental health support.

Participants will be sent an email and SMS invitation with a link to the online follow-up assessment at 8 weeks (T1) and 6 months (T2) post-randomisation and allocation to the intervention or comparison group. The 8-week survey will be available for completion for 2 weeks. At the end of the first week, an email and SMS reminder will be sent to those who have not completed the survey. The 6-month survey will be available for completion for 3 weeks, with two reminders sent to non-responders at one and 2 weeks.

Participants will be e-mailed a $30 voucher on completion of the study (i.e. complete baseline, 8-week and 6-month follow-up assessments) as a token of appreciation, and to aid recruitment and retention.

#### Randomisation

Participants will be randomised (1:1 ratio) to either the intervention (LISTEN) or comparison group (usual care), via central randomisation by computer. The allocation will be fully concealed from the research team including the project manager (RG) and the trial statistician (BH). Upon randomisation, participants will be notified of their group allocation via e-mail by a research assistant independent of the investigator team. Randomisation will be conducted in random permuted blocks of participants, stratified by diabetes type, gender and age (< 60; ≥ 60 years old), in order to minimise imbalances in the group allocation overall and on the specific strata. Once they are allocated to an available HP, participants randomised to the intervention arm will receive a call from the facilitating HP within 1 week (approx.) to arrange sessions. The research team (except SG who will be conducting quality assurance) will remain blinded. Any violation of blinding will be recorded and reported with the main findings.

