### Primary and secondary outcomes

All outcomes will be assessed pre-randomisation at baseline (T0), and post-randomisation at 8 weeks (T1) and 6 months (T2; primary endpoint).

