### Sample size

Based on a brief PST randomised pilot study assessing diabetes distress at 6 months [24] and assuming an alpha of 5%, we estimate requiring a minimum total sample of *N* = 226 (n = 113 per arm). This will enable us to detect an effect size of 0.3 (Cohen’s d) for the primary outcome, diabetes distress, with 80% power. Allowing for a 50% attrition rate observed in a trial with a similar recruitment strategy [47], we aim to recruit a minimum of *N* = 454 participants. Based upon prior experience using the NDSS register for recruitment to a trial [48], with a response rate of 1%, we estimate that recruiting a sample of *N* = 454 participants will require invitations to a random sample of *N* = 45,400 NDSS registrants.

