### Planned analyses

Analysis of the primary outcome will be conducted on an intention-to-treat (ITT) basis, using repeated measures analysis of variance (ANOVA), or restricted maximum likelihood mixed-effects models (REML) [49]. The null hypothesis, that there is no difference in the primary outcome between the intervention and comparison groups (at T2), will be assessed using *p*-values for the fixed-effects for the associated covariates in each model, with a *p*-value < 0.05 deemed statistically significant. If participants have missing assessments at T2, the analysis of variance will be replaced by a mixed model analysis using the REML. A per-protocol set (PPS) will include only those participants who engage with all aspects of the study protocol and complete a minimum of one LISTEN session (intervention) or access the web-based resource (comparison) to be used for a sensitivity analysis of the primary endpoint. Secondary outcomes, including psychological distress (K10), general emotional well-being (WHO-5) and coping self-efficacy (CSES) will be analysed as per the primary outcome.

Qualitative data from semi-structured interviews will be de-identified, transcribed verbatim using a professional transcriber and imported into NVivo. Thematic analyses [50] will be used to explore and identify key themes about participant’s experiences of the LISTEN intervention and barriers to, and facilitators of, adoption and implementation.

There are no plans to conduct an interim analysis of the outcomes, as per the statistical analysis plan. Due to the low-risk nature of the intervention, we do not anticipate any harm associated with the intervention for participants, and thus have no stopping rules.

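### The primary T2 analysis does not name baseline PAID or the stratification factors as adjustment terms; conditioning on them would gain precision at no cost

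*Protocol article*

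**What the plan says.** - **Protocol article, Randomisation.** Permuted blocks, "stratified by diabetes type, gender and age" (under 60, or 60 and over), at a 1:1 ratio.
- **Protocol article, Primary and secondary outcomes.** "All outcomes will be assessed pre-randomisation at baseline (T0), and post-randomisation at 8 weeks (T1) and 6 months (T2; primary endpoint"). A pre-randomisation PAID score is therefore available for everyone randomised.
- **Protocol article, Planned analyses.** The primary outcome is analysed by intention to treat "using repeated measures analysis of variance (ANOVA), or restricted maximum likelihood mixed-effects models (REML"). REML replaces ANOVA if T2 assessments are missing. The test of no difference at T2 uses p-values for fixed effects of covariates that the section does not name. K10, WHO-5 and CSES follow the same approach. The section does not say whether T0 is a response or a covariate, and it lists no stratification factor. It refers to a statistical analysis plan that is not shown.
- **Protocol article, Sample size.** 113 per arm are to "detect an effect size of 0.3 (Cohen’s d) for the primary outcome" with 80% power. "Allowing for a 50% attrition rate observed in a trial with a similar recruitment strategy", the target is 454. No baseline correlation or covariate adjustment is mentioned.

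**The concern.** The design pays for three prognostic factors through stratification and collects the variable likely to be the strongest predictor of the T2 score, but the described model commits to using none of them as adjustment terms. A repeated measures model over T0, T1 and T2 has a natural default: all three visits are responses and the group-by-time term is tested. At T2 that is a change-type contrast, which is less precise than conditioning on baseline at any correlation below 1. At low correlations it is even less precise than ignoring baseline.

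A low correlation is possible here, because eligibility requires raised PAID and a restricted baseline range tends to weaken the correlation. Precision also matters in this trial because 113 completers per arm leave none to spare. Leaving the choice open lets analyses with noticeably different power all claim to follow the plan.

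**Working it through.** **Inputs.** d = 0.3 (SD = 1), alpha 5%, 113 per arm at T2 and 454 recruited (227 per arm) are from Sample size; 1:1 allocation is from Randomisation. Assumed, because the document does not give them: a two-sided test, equal SDs at T0 and T2, dropout unrelated to outcome, and a T0–T2 correlation r of 0.4 to 0.6. T1 is ignored.

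**The plan's own figure.** An unadjusted comparison needs n = 2(1.960 + 0.842)²/0.3² = 174.4, so 175 per arm, not 113. At 113 per arm, SE = √(2/113) = 0.1330 and power = Φ(0.3/0.1330 − 1.960) = 61.6%. A one-sided 5% test would still need 138 per arm. The attrition step is sound: 226/0.5 = 452, against 454. The stated 80% therefore relies on precision from somewhere else.

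**Three ways to treat baseline.** Let V be the variance of the estimate per arm. Then power = Φ(0.3/√(2V) − 1.960).

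1. Baseline adjustment (covariate or constrained baseline): V = (1 − r²)/113.
2. Group-by-time contrast, T0 a response, completers only: V = 2(1 − r)/113.
3. Group-by-time contrast, T0 a response, REML using T0 from all 227 per arm: V = (1 − r²)/113 + (1 − r)²/227.

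With half the T2 scores expected to be missing, the plan's own switch to REML makes line 3 the relevant one if T0 is a response.

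Example at r = 0.5:
- Line 1: V = 0.75/113 = 0.00664, SE = 0.1152, power 74.0%.
- Line 2: V = 1/113 = 0.00885, SE = 0.1330, power 61.6%.
- Line 3: V = 0.00664 + 0.25/227 = 0.00774, SE = 0.1244, power 67.4%.

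| r (assumed) | No use of baseline | T0 as response, completers | T0 as response, REML, all T0 | Baseline-adjusted |
|---|---|---|---|---|
| 0.4 | 61.6% | 53.9% | 60.8% | 69.2% |
| 0.5 | 61.6% | 61.6% | 67.4% | 74.0% |
| 0.6 | 61.6% | 71.3% | 75.7% | 80.5% |

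Against the REML contrast, adjustment gains about 8, 7 and 5 points. Against a completers-only contrast it gains about 15, 12 and 9.

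**Correlation needed for 80%.** The required V is 0.3²/(2 × 2.802²) = 0.00573. Baseline adjustment reaches it at r = 0.59, the REML contrast at about 0.64 (0.00518 + 0.00056 = 0.00574 at r = 0.644), and the completers-only contrast at 0.68.

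**Strata.** If the strata explain a share R² of the T2 variance and the analysis is an unadjusted T2 comparison, actual type I error is 2[1 − Φ(1.960/√(1 − R²))]. An assumed R² of 5% gives 4.4%, and 15% gives 3.4%. Both lie below 5%, so the test is conservative. In a change-type contrast, stable differences between strata largely cancel and the effect would be smaller.

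**The case against.** The strongest reply is that this is a condensed article. Its analysis section foresees covariates without listing them, and covariate lists and the handling of baseline usually belong in the statistical analysis plan, which exists but is not shown. A reader might infer that the plan adjusts for none of these variables. The text does not support that: it is silent on how T0 enters, and both a baseline covariate and a constrained-baseline model fit its description of a REML mixed model. The assessment schedule is not a model specification. This part of the objection stands, and the point is worded accordingly.

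A second reply is that completers-only figures exaggerate the loss, because REML would use T0 from participants without T2. That also stands, and the REML column is the fair comparison. T1 data could narrow the gap further.

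A third is that the strata effect rests on an R² that the document does not give. That stands too.

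What remains is that the article does fix a model family, a T2 test and a sample size. The family as described admits contrasts that differ by 5 to 8 points of power, and the article does not commit to the more efficient one.

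**Conclusion.** The point holds as a worthwhile, costless improvement, not as a demonstrated error. If T0 is an ordinary response, conditioning on baseline PAID would raise power at T2 by about 5 to 8 points, from 61, 67 and 76% to 69, 74 and 80% at r = 0.4, 0.5 and 0.6. This rests on 113 completers per arm, d = 0.3, a two-sided 5% test, equal SDs, dropout unrelated to outcome, and an r that the document does not state. Most of the gain comes from baseline PAID. The strata matter mainly so that the standard error matches the randomisation.

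Two stronger readings are tempting and should be resisted:
- A reader might infer that 80% power is reachable only with baseline adjustment. It is not so: a completers-only change contrast also reaches it at r of about 0.68, and adjustment falls short of it below about 0.59.
- A reader might infer that omitting the strata makes the p-value untrustworthy. The departure is in the conservative direction, with no added risk of a false positive.

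The correlation that would justify 113 per arm is a separate matter for the Sample size section.

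**What to change.** Add to Planned analyses, and mirror in the statistical analysis plan before allocation is revealed to the statistician: the treatment contrast at T2 is estimated from a REML mixed model with baseline PAID as a covariate, or with baseline means constrained equal between arms, and with diabetes type, gender and age stratum (< 60, ≥ 60) as fixed effects. K10, WHO-5 and CSES are analysed in the same way, each with its own baseline value. Age may also enter as a continuous term. Name the T2 contrast as the quantity tested, in place of the reference to unnamed covariates. If the statistical analysis plan already says this, a cross-reference is enough.

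The cost is a sentence or two. Every variable is already collected at baseline or used at randomisation, and no change to recruitment, follow-up or data collection is needed.

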### LISTEN training for diabetes health professionals

HPs will be recruited via Diabetes Australia. A position description will be circulated internally as a first step. HPs will be volunteers and will complete a consent form prior to taking part in any aspect of the study. Eligibility criteria include Credentialled Diabetes Educator (or working towards credentialling) and Registered Nurse, Division 1 or Accredited Practising Dietitian; a minimum 12-month experience in Diabetes Education or working with people with diabetes in a community setting; an interest and motivation in supporting people with the emotional aspects of diabetes management; and experience providing structured education programs to consumers.

The HPs facilitating LISTEN will participate in comprehensive manualised training including (1) a 4-day online workshop and (2) supervised delivery of training cases. Following completion of the workshops, HPs will be allocated a minimum of two and a maximum of four training cases. Training cases are adults with diabetes who meet the inclusion criteria for the trial but who volunteer to be a ‘training case’. Sessions will be recorded and reviewed by a psychologist (SG) using the Problem-Solving Treatment Adherence and Competence Scale (PST-PAC) [30]. The PST-PAC examines fidelity to technical skills, adherence to the problem-solving steps, process tasks, communication and interpersonal effectiveness, and global competence based on the complexity of the client presentation. Fidelity is rated from 0 (*not completed*) to 5 (*well above standard*). Each session will be reviewed, and structured feedback provided to the HP during a weekly 1-h supervision session with SG, as well as unstructured discussions to promote micro-skills in session facilitation. To progress to the trial, HPs will be required to have completed ≥ 2 training cases, and achieved an overall PST-PAC score of ≥ 3 (*satisfactory*) for three consecutively-rated sessions, in accordance with an established PST training program [31].

### Intervention

The intervention group will receive up to four LISTEN sessions (45–60 min each), facilitated by a diabetes HP via telehealth. Sessions will be offered weekly to allow participants sufficient time to implement their action plan (*homework tasks*) between sessions. The core of LISTEN provides participants with a 6-step approach to addressing problems related to their diabetes that are contributing to their distress (see Fig. 3). Participants receive information and worksheets to support them between sessions to plan meaningful and enjoyable activities. Where appropriate, HPs will provide participants with a letter of attendance to take to their General Practitioner (GP referral letter) to help initiate a conversation about accessing further support from a mental health professional.

**Fig. 3 Fig3:**
[figure not shown]
The LISTEN intervention

### Comparison group

The comparison group will continue with their usual care and will receive a weblink to a freely available NDSS online factsheet about diabetes distress (https://www.ndss.com.au/wp-content/uploads/fact-sheets/fact-sheet-diabetes-distress.pdf), as well as links to general mental health support (e.g. Beyond Blue). They will also receive a general letter if they would like to discuss their emotional well-being with their GP.

During the trial, regardless of trial arm allocation, participants will not be asked to change their medications or diabetes management plan.

### Primary and secondary outcomes

All outcomes will be assessed pre-randomisation at baseline (T0), and post-randomisation at 8 weeks (T1) and 6 months (T2; primary endpoint).

#### Primary outcome

The primary outcome is the between-group difference in diabetes distress at T2. Diabetes distress will be assessed using the 20-item Problem Area in Diabetes (PAID) scale. Participants indicate which of the 20 diabetes issues are currently a problem for them, ranging from (0) ‘*not a problem*’ to (4) ‘*a serious problem*’. Item responses are summed and transformed to generate a scale score (0–100), with scores ≥ 40 indicative of severe diabetes distress. The PAID scale is valid, reliable and sensitive to change [32].

#### Secondary outcomes

General psychological distress will be assessed using the Kessler Psychological Distress Scale (K10). The scale contains 10 items about emotional states, rated on a five‐point scale, ranging from ‘*none of the time*’ to ‘*all of the time*’. The K10 score ranges from 10 to 50, with a higher score indicating greater psychological distress [33].

General emotional well-being will be assessed using the World Health Organization 5-item Well-being Index (WHO-5) [34]. Participants indicate symptom frequency over the past 2 weeks (0 = ‘*at no time*’ to 5 = ‘*all of the time*’). Item scores are summed and standardised to form a total score from 0 to 100. Higher scores represent better general emotional well-being.

Perceived ability to cope effectively with life challenges will be assessed using the Coping Self-Efficacy Scale (CSES) [35], which includes 26 items, each rated on a 11-point Likert scale, ranging from 0 (‘*cannot do at all*’) to 10 (‘*certain can do*’). Items form three subscales: problem-focused coping (12 items), stopping unpleasant emotions and thoughts (9 items) and getting support from family and friends (5 items), with higher scores indicating greater CSE. The total CSES scale score ranges from 0 to 260.

Generic health-related quality of life will be assessed using the 12-item Four-Dimensional Assessment of Quality-of-Life Instrument (AQoL4D) [36]. The scoring algorithm provides a total utility score on a scale from 0 to 1, based on Australian preferences for specific health states represented within the response items.

Information about the use of mental healthcare resources and lost productivity due to mental health problems will be captured using a Mental Health Resource Use and Productivity Impacts Questionnaire [37, 38].

The intervention group will also be invited to complete the Goal Attainment Scale [39]. At the beginning of their first LISTEN session, participants will set a goal for what they would like to achieve from the sessions. This will be recorded by the participant (or facilitating HP) on the PST worksheet. At the conclusion of their final session, participants will rate the extent to which their individual goals are attained (− 2 ‘*much less than expected*’ to + 2 ‘*much more than expected*’).

Demographic variables, collected at the baseline assessment (T0), include gender, age, education, marital status, employment status, mental health history and clinical characteristics (e.g. duration of diabetes, current treatment).

### Implementation outcomes

During the HP training and the RCT, we will use mixed methods to gather data on factors anticipated to affect the implementation of LISTEN, guided by the RE-AIM framework [40]. RE-AIM provides a structure for assessing health interventions beyond efficacy, with a focus on translatability into real-world settings.

#### Reach

Response rates, number of eligible participants and time to recruit the target sample will be monitored via the online registration system (Qualtrics). To determine whether participants are representative of people with diabetes in Australia, we will examine response rates by diabetes type, gender, age group, and geographical location (i.e. regional/remote areas). The number of eligible participants engaging in at least one LISTEN session will be monitored by an audit of the study database.

#### Effectiveness

Intervention effectiveness will be evaluated using a RCT (described above).

#### Adoption and implementation

##### Intervention fidelity

We will audit a random selection (20%) of LISTEN session audio recordings, stratified by HP and session number (1–4), to assess HPs’ fidelity to the program content (i.e. PST steps) and therapeutic techniques. Sessions will be rated independently (using the PST-PAC) by two experienced researchers and fidelity scores discussed until consensus is reached.

##### LISTEN training evaluation

HPs will be invited to complete three brief online surveys to explore satisfaction with the LISTEN training program as well as changes in confidence and motivation to facilitate sessions. The surveys will be (1) on entry into the study (baseline/pre-training), (2) following the LISTEN workshops, and (3) following the completion of their supervised training. Acceptability and satisfaction ratings are guided by the PRECEDE–PROCEED Model [41] and adapted from a previous published evaluation of health professional training in brief PST [42].

##### Intervention acceptability

Acceptability of LISTEN to participants in the intervention group, and their suggestions for improving sessions, will be explored using: (1) rating scales and open-ended questions at 8-week follow-up (T1); and (2) via semi-structured interviews with a random sample of 20–30 participants who undertake ≥ 1 LISTEN session). The random sample will be stratified to include a range of participants (e.g. by diabetes type, age, gender, number of sessions completed). The interview schedule is informed by the Theoretical Framework of Acceptability (TFA) [43] and adapted from a published interview exploring the acceptability of brief PST [21].

##### Barriers to, and facilitators of, adoption and implementation

We will conduct semi-structured interviews with 5–15 key stakeholders (i.e. HPs who facilitate LISTEN during the trial, representatives from Diabetes Australia and Diabetes Victoria involved in the study) to explore barriers and facilitators encountered during the HP training, LISTEN delivery and implementation strategies tested during the trial (Table 1). The interview schedule is aligned with the five Consolidated Framework for Implementation Research (CFIR) [44] domains. This will be supplemented with field notes (e.g. strategies discussed during supervision sessions with HPs to enhance intervention facilitation, strategies to enhance participant engagement and completion of LISTEN).

**Table 1 Tab1:** Implementation strategies^a^ tested in the LISTEN trial

Strategy	Target	Stage of LISTEN study	Description and dose	Intended effect
Training materials and worksheets	HPs	HP training/trial	Training materials and worksheets will be provided to HPs during the LISTEN workshops, refined for trial (as needed)	Enhance skills acquisition and facilitation of LISTEN
Supervision	HPs	HP training/trial	Training: weekly individual 1-h sessions Trial: monthly individual 30-min sessions + ad hoc group sessions. All supervision will be provided by a psychologist (SG)	Enhance skills acquisition and facilitation of LISTEN, provide support and encouragement, promote intervention fidelity
Between supervision communication	HPs	Trial	As needed. Via e-mail, meetings, newsletters	Monitor HP scheduling to ensure a steady flow of participants are allocated to the intervention; maintain HPs motivation as a LISTEN facilitator (e.g. feedback from participants on the
Recruitment and promotional materials	Participating adults with diabetes	Trial	Refinements will be made to the recruitment/promotional materials in response to incoming data. This includes language used in recruitment flyer, short video, LISTEN information leaflet, social media posts	Increase enrolment of eligible participants into the trial
Processes and procedures	Participating adults with diabetes			Enhance engagement

^a^Implementation strategies are described according to recommendations published by Proctor et al. (2013) [29]

